### Participant Recruitment and Screening

2.3

Between September 2025 and March 2026, DM with PHP were recruiting from three hospitals in Jashore, Bangladesh. Participants were screened for eligibility by two trained research assistants, and those who met the criteria provided written informed consent. Following CONSORT guidelines, participants were randomly assigned to their allocated groups using a concealed allocation method. Four blinded assessors conducted baseline assessments prior to the intervention's commencement. The intervention follows a standardized, concealed protocol, with participants blinded to group allocation to minimize bias.

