### Study Design

2.1

This study was a multicenter, parallel, assessor‐ and participant‐blinded randomized clinical trial with an 8‐week intervention period, conducted at the Nurul Islam Diabetic Centre, Ibn Sina Diabetes Centre, and City Hospital & Diabetic Care, Jashore, Bangladesh, from September 2025 to March 2026. Eligible participants were randomly assigned in a 1:1 ratio to either the SDM or MFR group. This trial has been designed following the Standard Protocol Items: Recommendations for Interventional Trials (SPIRIT) guidelines, which offer a comprehensive framework for developing RCT protocols, as detailed in Table 1. Additionally, the Consolidated Standards of Reporting Trials (CONSORT) statement has been adopted to improve the quality and completeness of RCT reporting, as shown in Figure 1.

**Table 1 hsr272255-tbl-0001:** SPIRIT table.

Timepoint	Enrollment	Allocation		Post‐allocation	
	−*T* _1_	*T* _0_	*T* _1_	*T* _2_	*T* _3_
*Enrollment*					
Eligibility screening	X				
Informed consent		X			
Demographic and clinical assessment			X		
Group allocation		X			
*Intervention*					
SDM Group			X	X	
MFR Group			X	X	
*Assessment*					
Pain intensity			X	X	X
Range of motion			X	X	X
Muscle strength			X	X	X
Foot Function Index			X	X	X

*Note:* −*T*
_1_, prestudy enrolment; *T*
_0_: group allocation; *T*
_1_, baseline before intervention; *T*
_2_, measurement after 8 weeks; *T*
_3_, measurement after 20 weeks.

Abbreviations: MFR, myofascial release; SDM, Structural Diagnosis and Management.

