### Outcome Measurements

2.7

Baseline sociodemographic and clinical characteristics were collected immediately after obtaining informed consent from participants and before the initiation of the intervention. All primary and secondary outcomes were planned to analyze at three time points: baseline (Week 0), posttest (Week 8), and follow‐up (Week 20), by four trained and blinded assessors.

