## Discussion

3

The primary aim of this study is to evaluate the effectiveness of the SDM Approach versus MFR in treating PHP in diabetic patients. Previous research indicates that approximately one million individuals are referred annually to a doctor for a definitive diagnosis of plantar fasciitis. A recent cohort study identified the prevalence of plantar fasciitis as 720,000, with an incidence of 0.85% among diabetic patients [8, 9, 10, 11, 12]. Several studies have explored various interventions that could provide interim relief from PHP, plantar fasciitis, and heel spurs, such as considering and providing anti‐inflammatory agents, electrical modalities, and manual therapies like nerve mobilization, often focusing solely on the central pain area rather than the affected structures [14, 15].

However, our study considers the potential scope by including the associated structures, which may be a more critical factor in achieving sustainable outcomes. Without addressing these, diabetic patients are increasingly at risk of this foot condition, which often remains untreatable and misunderstood. To date, no research has directly compared and analyzed yet the effectiveness of SDM versus MFR in treating PHP in people with diabetes mellitus. The long‐term objective of this study is to play a vital role in the management of this global condition.

This study offers several significant benefits. It marks the first attempt in Bangladesh to compare the effectiveness of SDM and MFR in managing PHP among individuals with diabetes mellitus, incorporating a 12‐week follow‐up period. The study highlights the potential contribution of these intervention strategies not only in reducing pain but also in improving functional outcomes that enhance patients' quality of life. By addressing a significant gap in existing research, this study may offer valuable insights for clinical practice and future research in DF management.

However, limitations include the focus on a specific area in Bangladesh, which may restrict the broader applicability of its findings. Additionally, the presence of multiple comorbidities and a limited sample size are notable constraints. Future research should involve a larger and more diverse population, with an extended follow‐up duration. It is also recommended that subsequent studies adopt more rigorous research designs, suited to resource‐limited settings, to enhance the validity and generalizability of the findings.

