## Study Status

4

This randomized clinical trial is currently recruiting participants and is expected to be completed within the preplanned timeline.

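### Recruitment and the whole trial are given the same dates, September 2025 to March 2026, which the 20-week follow-up does not fit

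*Protocol article*

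**What the plan says.** Section 2.1 (Study Design) states that the trial was conducted at the three centres "from September 2025 to March 2026". Section 2.3 (Participant Recruitment and Screening) gives the identical period for enrolment: "Between September 2025 and March 2026, DM with PHP were recruiting from three hospitals in Jashore, Bangladesh".

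The visit schedule is fixed per participant. The note to Table 1 defines the last assessment as "measurement after 20 weeks", and section 2.7 (Outcome Measurements) counts from baseline as Week 0, with the post-treatment visit at Week 8 and follow-up at Week 20. The Discussion agrees with this count, describing the trial as "incorporating a 12‐week follow‐up period" after the 8-week treatment.

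Section 4 (Study Status) says the trial "is currently recruiting participants and is expected to be completed within the preplanned timeline". No section gives a separate last-enrolment date or a later date for the end of follow-up. Section 2.15 (Data Analysis) handles missing data by last observation carried forward (LOCF).

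**The concern.** A trial with 20 weeks of follow-up must run at least 20 weeks beyond its last enrolment. Here one seven-month window has to serve as both the recruitment period and the life of the trial, so at least one of the two statements is wrong as printed.

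The statistical stake lies in what happens if March 2026 is taken literally as the end. Participants with a late baseline would then lack a Week-20 score for a purely administrative reason, and the latest of them would lack a Week-8 score too. Under the LOCF rule, a missing Week-20 score would be replaced by the Week-8 score. Where Week 8 is also missing, both visits would take the baseline score, which imputes no change in pain, the primary outcome. The aim of examining sustained effects (Abstract) and the third objective (Introduction), which compares follow-up outcomes, depend on real Week-20 data.

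**Working it through.** **Inputs from the article**
- Recruitment window: September 2025 to March 2026 (section 2.3), read as 1 September 2025 to 31 March 2026.
- Conduct window: the same months (section 2.1).
- Visits: Week 8 (56 days) and Week 20 (140 days) after baseline (section 2.7; Table 1). Check on the count: 8 weeks of treatment + 12 weeks of follow-up = 20 weeks.
- Planned enrolment: 90 (section 2.2).

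**Length of the window.** 1 September 2025 to 31 March 2026, both days included, is 30 + 31 + 30 + 31 + 31 + 28 + 31 = 212 days, about 30 weeks. Recruiting through all of it and then following the last participant for 20 weeks takes about 30 + 20 = 50 weeks.

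**Latest baseline that fits** (end of window minus visit time)
- Week 20: 31 March 2026 − 140 days = 11 November 2025.
- Week 8: 31 March 2026 − 56 days = 3 February 2026.

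These are the most generous cut-offs. If the window ended on 1 March 2026, each moves back 30 days, to 12 October 2025 and 4 January 2026.

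**When visits would end if recruitment runs to 31 March 2026**
- Last Week-8 visit: 31 March + 56 days = 26 May 2026.
- Last Week-20 visit: 31 March + 140 days = 18 August 2026.

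**How many participants fit inside the window.** The article gives no accrual rate, so the figures below are illustrations under assumptions. Let p be the fraction of the window that has passed at the cut-off: 72/212 = 0.340 for Week 20 and 156/212 = 0.736 for Week 8.
- Uniform accrual (share = p): Week 20, 0.340 × 90 ≈ 31; Week 8, 0.736 × 90 ≈ 66.
- Front-loaded, rate falling linearly to zero (share = 1 − (1 − p)²): Week 20, 1 − (140/212)² = 0.564, about 51 of 90; Week 8, 1 − (56/212)² = 0.930, about 84 of 90.
- Back-loaded, rate rising linearly from zero (share = p²): Week 20, (72/212)² = 0.115, about 10 of 90; Week 8, (156/212)² = 0.542, about 49 of 90.

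For all 90 to fit, enrolment would have to be complete by 11 November 2025. That needs 90/(72/7) = 8.75 per week, against 90/(212/7) ≈ 3.0 per week if recruitment used the whole window.

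**The case against.** The best defence is that section 2.1 loosely repeats the enrolment dates and that follow-up simply continues to about August 2026. Sections 2.7 and 2.11 schedule the Week-8 and Week-20 assessments with no calendar cut-off, and nothing says that visits stop or the database closes in March 2026. On that reading no data are lost. This stands as far as the consequence goes: the loss of data is conditional. It does not remove the inconsistency, because section 2.1 attaches the dates to the conduct of the trial and the end of follow-up is then given nowhere.

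Four stronger readings are tempting, and the article does not support them.
- A reader might infer that most Week-20 scores will be carried-forward values. That needs both closure in March 2026 and an accrual pattern that the article does not give. The three patterns above put the share reaching Week 20 in time anywhere from about 12% to 56%.
- A reader might take section 4 as a separate promise to finish by March 2026. It names no end date, and becomes a conflict only when the dates in section 2.1 are read into it.
- A reader might take publication on 2 April 2026, with recruitment still reported open, as proof of an overrun. The status text may date from submission.
- A reader might conclude that no between-arm analysis may be run before the last Week-20 visit. That does not follow from a date conflict. Section 2.14 allows the monitors interim analyses, which is a separate matter.

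That an article condenses a fuller protocol is no answer here: the problem is two printed dates that do not fit the printed visit schedule, not an omitted detail.

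**Conclusion.** The timeline is wrong as written. With recruitment and conduct both dated September 2025 to March 2026, a Week-20 visit inside the window is possible only for baselines up to 11 November 2025, and a Week-8 visit only for baselines up to 3 February 2026. Recruiting through March 2026 implies follow-up to about 18 August 2026, some 50 weeks in all against the 30 stated. These dates assume that the window ends on 31 March and that baseline falls on the day of enrolment.

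The effect on the data is conditional. It arises only if the trial closes as dated, and its size depends on accrual: about one third of 90 would reach Week 20 in time under uniform enrolment, more if front-loaded and fewer if back-loaded. This is an internal timeline inconsistency of moderate severity. The article gives no sign that truncated follow-up was chosen as a design.

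**What to change.** State the end of recruitment and the end of follow-up as two separate dates. Set the end of the trial and the final analysis no earlier than last enrolment plus 20 weeks: about 18 August 2026 if recruitment ends on 31 March 2026, and later if it continues. Reconcile sections 2.1 and 2.3 to these dates, and make clear which end date the timeline mentioned in section 4 refers to.

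The cost is a correction of dates. It adds no visits and leaves the sample size and analysis methods unchanged, since the 20 weeks are already in the visit schedule. Whether the registry and ethics records carry the same dates cannot be seen from the article; if they do, they should be updated to match.

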### Eligibility Criteria

2.4

Participants were screened for eligibility by trained research assistants. Inclusion criteria: (1) age between 30 and 65 years for both male and female [17]; (2) participants diagnosed with unilateral or bilateral heel pain or plantar fasciitis (according to ICD‐10 criteria, ICD diagnosis codes M72.2); (3) localized pain in the plantar region of the foot when placed their barefoot on the floor in the morning; (4) ankle dorsiflexion is more limited than plantar‐flexion; and (5) suffering with PHP from more than 4 weeks [17]. Exclusion criteria: (1) confirmation and diagnosis of diabetic peripheral neuropathy; (2) history of lower extremity fracture, rheumatoid arthritis, osteoarthritis, carcinoma, surgery of the foot, and metal implant around ankle [15]; (3) active foot ulceration, infection, severe peripheral vascular disease, gangrene of the foot, cyanotic symptom, and severe neurological condition [11]; (4) contraindicated to manual therapy or exercise intervention [17]; and (5) participants taken corticosteroids injection within 6 months [16].

### Randomization and Blinding

2.5

Eligible participants with written informed consent were randomly allocated to their respective groups, either the SDM or the MFR group. The randomization sequencing process was conducted using the “Rand” function in Microsoft Excel 2013 software. A sequential list of participants' IDs, sorted according to the randomly generated numbers. This procedure helps to prevent bias. Participants were allocated to a parallel intervention group in a 1:1 ratio. This is an assessor‐ and participant‐blinded randomized clinical trial, with outcome assessors and participants blinded to group allocation. Physiotherapists delivering manual therapy could not be blinded, but both groups received identical conventional physiotherapy to control for nonspecific effects. Therapists were trained to follow standardized protocols and avoid discussing treatment or outcomes with participants or assessors to minimize bias. Inter‐rater reliability for manual techniques will be established, and any unblinding will be documented and reported.

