### Data Analysis

2.15

Data analysis will be performed by an independent statistician using SPSS version 22, with anonymized and encrypted data to ensure confidentiality. Prior to analysis, data will be screened for completeness and outliers. The parametricity of the data will be assessed using the Kolmogorov–Smirnov and Shapiro–Wilk tests, supported by evaluation of skewness and kurtosis and visual inspection of data distribution through histograms and normal probability plots. Descriptive statistics, including mean and standard deviation for normally distributed variables, median and interquartile range for non‐normally distributed variables, and frequency and percentage for categorical variables, will be used to summarize continuous and categorical data. Baseline characteristics, including body mass index and duration of diabetes, will be reported to assess group comparability, and exploratory subgroup analyses for high‐risk participants will be considered if clinically relevant patterns are observed. For comparisons across three time points (baseline, postintervention, and follow‐up), repeated‐measures ANOVA will be applied for normally distributed data, with the Friedman test used as the nonparametric alternative. Between‐group and within‐group differences will be analyzed using independent and paired *t*‐tests for parametric data, or Mann–Whitney *U* and Wilcoxon signed‐rank tests for nonparametric data, as appropriate. The laterality of PHP (unilateral or bilateral) will be recorded and incorporated into the analysis to minimize potential confounding effects on ROM and muscle strength outcomes. Effect estimates and mean differences will be reported with 95% confidence intervals alongside *p* values. All statistical tests will be two‐tailed, with statistical significance set at *p* < 0.05, *p* < 0.01, and *p* < 0.001. In addition, baseline, posttest, and follow‐up change scores will be evaluated, and an intention‐to‐treat analysis using the last observation carried forward method will be applied to handle missing data and preserve the validity of the analysis.

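### Three-hospital trial with no centre stratification named in the allocation and no centre term in the between-arm tests: a cheap loss of precision, not a bias

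*Protocol article*

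**What the plan says.** The Study Design section says the trial was "conducted at the Nurul Islam Diabetic Centre, Ibn Sina Diabetes Centre, and City Hospital & Diabetic Care, Jashore, Bangladesh", and the recruitment section repeats that participants "were recruiting from three hospitals in Jashore, Bangladesh". The share of the 90 participants expected from each hospital is not given.

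On sequence generation, the Randomization and Blinding section gives the tool, "The randomization sequencing process was conducted using the “Rand” function in Microsoft Excel 2013 software", then the list, "A sequential list of participants' IDs, sorted according to the randomly generated numbers", and the ratio, "Participants were allocated to a parallel intervention group in a 1:1 ratio". One list is described; strata and blocks are not mentioned. The recruitment section adds that allocation was concealed.

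On analysis, the Data Analysis section states: "Between‐group and within‐group differences will be analyzed using independent and paired" *t*-tests, with Mann–Whitney U and Wilcoxon signed-rank as the non-parametric alternatives. Repeated-measures ANOVA or Friedman tests cover the three time points. The only factor to be built into the analysis is laterality of heel pain, and that for range of motion and strength. Centre is not named for any outcome, including the primary VAS.

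**The concern.** Centre is known for every participant at no cost, and in a hands-on physiotherapy trial it is a foreseeable source of outcome variation. A 1:1 split of one list balances the arms 45:45 overall but does not hold the balance within each hospital. If the hospitals differ in average outcome, an uneven split shifts the observed arm difference by chance, and a two-sample test with no centre term cannot correct for it. The same test also leaves the between-hospital variation in its residual, which widens the confidence interval. At stake is the precision of the VAS comparison in a trial with little to spare: if the planning effect of 0.50 is read as a standardised mean difference, 45 per arm gives about 65% two-sided power before any centre variation is added.

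**Working it through.** **Inputs from the article.** Three centres; 90 participants, 45 per arm; 1:1 from one list; two-sided 5% tests; effect size 0.50, read here as a standardised mean difference.

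**Assumptions, because the article gives no figures.** Centre sizes of 30/30/30 (with 50/25/15 and 60/20/10 as alternatives); centre means spanning 0.5 or 1 within-centre SD, equally spaced; all 90 analysed.

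**1. Chance imbalance.** With one 45:45 list, the number of SDM participants in a 30-person centre is hypergeometric:

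- mean = 45 × 30/90 = 15
- SD = √[45 × (1/3) × (2/3) × (45/89)] = √5.06 = 2.25

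A 60:40 split in a centre of 30 means 18:12 or worse. Taking the three centres jointly:

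| Centre sizes (assumed) | At least one centre 60:40 or worse | At least one centre 2:1 or worse |
|---|---|---|
| 30/30/30 | 50% | 11% |
| 50/25/15 | 71% | 30% |
| 60/20/10 | 85% | 36% |

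**2. Effect on the estimated arm difference (30/30/30).** The mean shift is 0. Its SD is 0.04 SD units, with 95% of allocations within 0.09, if centre means span 0.5 SD. If they span 1 SD, the SD is 0.09 and the 95% limit 0.18.

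**3. Type I error and power (simulation, 10,000 runs per cell, 30/30/30, true difference 0.5 SD for power).**

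| Allocation and analysis | Type I error, span 0.5 SD | Power, span 0.5 SD | Type I error, span 1 SD | Power, span 1 SD |
|---|---|---|---|---|
| One list, no centre term (as described) | 5.1% | 62.5% | 5.0% | 57.7% |
| One list, centre term | 5.2% | 64.4% | 5.3% | 64.1% |
| Stratified, no centre term | 4.6% | 63.0% | 3.7% | 59.1% |
| Stratified, centre term | 4.7% | 64.7% | 5.0% | 64.4% |

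The Monte Carlo standard error of each power figure is about 0.5 percentage points: √(0.625 × 0.375/10,000).

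**4. Check by formula.** Without a centre term the residual variance is about 1 + 2(span/2)²/3. That is 1.042 for a span of 0.5 and 1.167 for a span of 1, so the effective standardised difference falls from 0.50 to 0.50/√1.042 = 0.490 or 0.50/√1.167 = 0.463. With 45 per arm, non-central t power is 63.2% and 58.4% respectively. With the centre variation removed it is 65.0%. These agree with the simulation to within about one percentage point.

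Nearly all the gain comes from the centre term. Stratification adds a few tenths of a point on top, which is within simulation error.

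**The case against.** The strongest reply is that this reads silence as method. The article never says outright that allocation was unstratified, it is a condensed account, and a centre term could sit in a full protocol or analysis plan that is not shown. That stands as a caution. But the article goes into enough detail to give the software and the sorting step, and it names the between-arm tests. A centre term would change those tests, not merely fill in detail.

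Second, unstratified randomisation is valid. This also stands: the expected shift is zero and the type I error stays near 5%. A reader might infer that leaving out centre biases the treatment comparison; the calculations do not support that. Nor does the article give evidence that the hospitals differ, and all three are diabetic centres in Jashore.

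A reader might also go further in three ways that the text does not support:

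- **Therapist confounding.** The article does not give the number of therapists, where they work, or whether each treats one arm or both. It does report that "Therapists were trained to follow standardized protocols and avoid discussing treatment or outcomes with participants or assessors to minimize bias", and it plans to establish inter-rater reliability for the manual techniques. If therapists were tied to one arm, stratifying by centre would not remove the problem.
- **A sequence that could not have been predetermined.** Study numbers can be listed before anyone enrols, so sorting a list of IDs is compatible with the predetermined sequence in the Study Procedure section. Nothing suggests that the list was re-sorted during recruitment.
- **The 85% figure as a headline.** It is mostly small-centre arithmetic. A 6:4 split in a 10-person centre counts as 60:40, and that centre alone meets the criterion in about 74% of allocations, with little effect on the overall arm difference.

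Finally, recruitment was planned to end in March 2026 and the article appeared on 2 April 2026, although its status section still reports recruitment as ongoing. A change to allocation may therefore reach few participants. The analysis change is unaffected.

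**Conclusion.** The point holds as a modest, inexpensive improvement. As described, the plan leaves chance centre imbalance uncorrected and between-centre variation in the error term of the VAS comparison. With 30 per centre, a 60:40 or worse split in at least one hospital is about as likely as not. Stratification plus a centre term would gain about 2 percentage points of power (62.5% to 64.7%) if centre means span 0.5 SD, and about 7 (57.7% to 64.4%) if they span 1 SD. These figures rest on assumed centre sizes, assumed centre differences, all 90 participants analysed, and the planning effect read as a standardised difference of 0.5. If the hospitals hardly differ, the gain is close to nil. The validity of the randomisation is not in question.

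**What to change.** In the Data Analysis section, make the between-arm comparison of VAS and of each secondary outcome a linear model with arm and centre as fixed factors, and report the arm difference with its 95% confidence interval from that model. Report arm counts by centre. This can be done whatever the state of recruitment, provided it is fixed before the analysis.

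For any participants still to be randomised, use a separate pre-generated list for each centre with varying block sizes. Pair this with the centre term: stratifying without it makes the test conservative (type I error 3.7% when centre means span 1 SD).

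The cost is two degrees of freedom (86 residual instead of 88 with all 90 analysed) and the short time needed to generate three lists. No extra participants or data are needed.
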